### Sample size

Estimating the mean number of hospital inpatient days is 42 for those receiving standard care and 36 for those receiving monitoring, assuming a standard deviation of 10 and 40 patients per arm, approximate 95% confidence intervals for these estimates would be (39, 45) and (33, 39) respectively. To allow for patient drop out a total of 100 patients will be recruited (50 patients in each group).

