**Fig. 1 Fig1:**
[figure not shown]
Flow of patients through the study

Participants will be screened from the West Midlands Adult CF Centre database by the study investigators. If eligible, the study investigators will approach patients when they are attending routine clinic visits or during inpatient admissions to explain the study and if they are potentially interested they will be given the Participant Information Sheet. Having had time to consider the study and have any questions answered to their satisfaction, patients still keen to take part will be asked to provide written informed consent. It will be explained that they may withdraw from the study at any time.

At this point, baseline data will be obtained and the participant will be asked to take part in a semi-structured qualitative interview to assess the patient experience of their care to date and their expectations of participating in the study. Within strata, participants will then be randomly assigned to receive either home monitoring or routine care. The strata are based on the number of hospital admissions to receive intravenous antibiotics over the preceding 24 months, separated into four strata: ‘1–2 admissions’, ‘3–4 admissions’, ‘5–6 admissions’ and ‘more than seven admissions’. The randomisation will be completed by the selection of randomly ordered sealed opaque envelopes, with randomisation having been performed by a clerical member of the CF team with no knowledge of the study.

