## Interventions

### Routine care group

These participants will continue to receive routine CF care, including regular outpatient clinic appointments and inpatient admissions if required.

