### Home monitoring group

Participants randomized to receive home monitoring will be provided with a Bluetooth-enabled digital spirometer and a ‘Microsoft Windows Mobile’ enabled mobile phone. Participants will be shown how to use the equipment before going home. Participants will be asked to record their FEV_1_ using a digital spirometer twice weekly (Monday and Thursday), which will take around 5 min to complete. Participants will also record their symptoms twice weekly (Monday and Thursday) on the mobile phone by completing the Cystic Fibrosis Respiratory Symptom Diary – Chronic Respiratory Infection Symptom Score (CFRSD-CRISS) [5]. This is a validated disease-specific tool (consisting of 16 questions) designed to detect symptoms of pulmonary exacerbations in CF, taking around 5 min to complete.

Data regarding lung function and symptoms will be automatically transmitted via a secure encrypted wireless connection and the research team will be able to access this data instantaneously on a specially designed website. The mean values of the first 2 weeks’ data will be used to determine the participants’ baseline levels for FEV_1_ and CFRSD-CRISS during the run-in phase. Following this initial 2-week period, the CF team will receive an email alert if participants’ FEV_1_ or symptoms deteriorate below a set threshold. The criteria that will trigger an email alert are one of: 1) a drop in FEV_1_ of 10% or more from baseline; 2) total score of the CFRSD-CRISS worsening by more than three points from baseline. Following an email alert, the CF team will contact the participant within 24 h to discuss their symptoms. Based on this discussion, the research team will advise the participant on the best management. If the participant needs to be assessed in the outpatient clinic, we will arrange the next available convenient appointment. Depending on the clinical assessment, participants will receive a course of antibiotics, either oral or intravenous depending on the severity of symptoms, sputum microbiology and patient choice. If prescribed antibiotics, we will document whether these were prescribed for a protocol-defined pulmonary exacerbation (see definition below).

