To minimize lack of adherence to home monitoring, we will re-enforce the importance of adhering to the study protocol at each study visit. The system will alert the research team if any participant fails to record symptoms and spirometry data. If this occurs, we will call the participant to check if they are having any problems with the equipment and that they are willing to proceed with the study. If there are any difficulties with using the equipment, we will explain how to resolve this issue. If any participant fails to submit data for more than 20% of occasions over any 28-day period we will advise them that they risk being withdrawn from the study. If there was a good reason for them not to submit data (such as a foreign holiday of which we were not aware) we will remind them to inform us if they will not be able to submit data. If the lack of data was due to non-adherence to the study protocol and if the participant fails to submit data for more than 20% of a subsequent 28-day period they will be withdrawn from the study. If the participant does not wish to proceed with the study at any stage they will be withdrawn and this will have no adverse effect on their routine care.

In addition to recording their symptoms and spirometry, subjects receiving home monitoring will be asked to test a urine sample once every week and send a urine sample in a prepaid envelope. These samples will be batched and subsequently analysed for biomarker analysis and this data will not be used by the research team during the course of this study.

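### Repeated non-adherence to home monitoring leads to withdrawal from the study, a rule only the monitored arm can trigger, so both primary outcomes are at risk of differential loss

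*Protocol article*

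**What the plan says.** All references are to the protocol article.

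- **Schedule (Home monitoring group).** "Participants will also record their symptoms twice weekly (Monday and Thursday) on the mobile phone"; home spirometry falls on the same two days.
- **First breach (same section).** A warning goes to anyone who "fails to submit data for more than 20% of occasions over any 28-day period we will advise them that they risk being withdrawn". Before that, the team telephones when data are missing and helps with equipment problems. A gap with a good reason brings only a reminder.
- **Second breach (same section).** This step applies only where the earlier gap is put down to non-adherence. Its consequence is stated outright: "if the participant fails to submit data for more than 20% of a subsequent 28-day period they will be withdrawn from the study".
- **Control arm (Routine care group).** "These participants will continue to receive routine CF care, including regular outpatient clinic appointments and inpatient admissions if required". No home readings are asked of this group.
- **Voluntary withdrawal (Recruitment and randomisation).** All participants are told of this before allocation: "It will be explained that they may withdraw from the study at any time".
- **Outcomes (Outcome measures).** Both primary outcomes, inpatient bed days and CFQ-R, are recorded at visits up to 12 months.
- **Sample size.** The assumptions are means of 42 and 36 days, an SD of 10 and 40 patients per arm. "To allow for patient drop out a total of 100 patients will be recruited (50 patients in each group".
- **After withdrawal.** The only provision in the article is in Qualitative analysis: follow-up interviews may explore why someone left.

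**The concern.** The rule makes staying in the trial depend on behaviour after randomisation that exists in one arm only. A control cannot fail to submit home data. If withdrawal ends the study visits, the monitored arm loses its persistent non-adherers while the control arm keeps their counterparts. The comparison then drifts towards adherent monitored patients against all controls.

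The article's hypothesis, at the end of Background, is about participants allocated to home monitoring, so the effect by allocation is what it sets out to learn. The planned cost per bed day reduced and cost per QALY would carry the same selection. The qualitative work is meant to explain differing use of monitoring, and low users are the people the rule removes.

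**Working it through.** **1. The plan's own figures.** With SD 10 and n = 40, the half-width is 1.96 × 10/√40 = 3.10. This gives 42 ± 3.10 = (38.9, 45.1) and 36 ± 3.10 = (32.9, 39.1), which round to the stated (39, 45) and (33, 39). Recruiting 50 to evaluate 40 implies a loss of 1 − 40/50 = 20%, the same in each arm and for all causes.

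**2. The threshold.** Two occasions a week over four weeks is 8 per 28 days. One miss is 12.5% and two are 25%, so two or more misses exceed 20%. That brings a warning. Withdrawal needs a further breach in a later period.

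**3. How often two breaches could occur (assumed submission rates).** Let q be the chance of missing an occasion, with misses independent and none excused. Then P(breach) = 1 − (1−q)^8 − 8q(1−q)^7, and two breaches means at least 2 of 13 separate 28-day windows.

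| Submission rate | P(breach in one window) | P(at least 2 of 13 windows) |
|---|---|---|
| 95% | 5.7% | 16.8% |
| 90% | 18.7% | 72.9% |

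These are upper-side illustrations, because telephone calls, the warning and excused gaps all lower them. They are not strict bounds: the warning can arise over any 28-day period, and overlapping windows would push the other way.

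**4. Bias if withdrawn participants drop out of the comparison (assumed inputs).** Take no true effect, a mean of 42 in both arms and 20% of the monitored arm removed. If those removed have r times the bed days of those kept, the kept mean is k = 42/(0.8 + 0.2r) and the apparent benefit is 42 − k. The share of variance that non-adherence must explain is 0.2 × 0.8 × gap²/10², where gap is the difference between the removed and kept means.

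| r | Kept mean | Removed mean | Apparent benefit | Share of variance at SD 10 |
|---|---|---|---|---|
| 1.25 | 42/1.05 = 40.0 | 50.0 | 2.0 days | 0.16 × 10.0²/100 = 16% |
| 1.5 | 42/1.10 = 38.2 | 57.3 | 3.8 days | 0.16 × 19.1²/100 = 58% |

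The second row asks a great deal of adherence as a predictor. In the other direction, if those removed use 5 fewer days than those kept, the kept mean is 42 + 0.2 × 5 = 43, an apparent harm of 1.0 day.

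**5. Artefact if bed days are counted only to withdrawal, with no time adjustment.** For 20% withdrawn at mid-year, 42 × 0.20 × 0.5 = 4.2 days in favour of monitoring. Across 10% to 30% withdrawn at 75% to 25% of follow-up, the range is 42 × 0.10 × 0.25 = 1.05 to 42 × 0.30 × 0.75 = 9.45 days.

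**6. What that does to a test.** With 50 against 40 analysed, SE = 10 × √(1/50 + 1/40) = 2.12. A bias of 1 or 2 days raises a two-sided 5% error rate to 7.6% or 15.6%. The loss of numbers matters much less: power for 6 days is about 81% at 50 v 40 and 85% at 50 v 50.

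**7. CFQ-R.** The article gives no figures from which to size the effect. Scores are self-reported at visits, so those not collected cannot be recovered later.

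**The case against.** **The article is a condensed document.** The full protocol or SAP may keep withdrawn participants in follow-up and analyse by allocation. That is fair, and the lack of a named analysis set is not part of this point. What remains is a rule that the article does state. An analysis set defined elsewhere cannot supply CFQ-R scores that were never taken.

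**The safeguards are real.** A call, help with equipment, a warning, a good-reason exemption and a second breach all come before withdrawal, so two missed readings alone remove nobody. They reduce the number affected but do not change who can be affected. The research team also judges what counts as a good reason, in a non-blinded trial.

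**A reader might infer that the bed-day comparison is biased towards monitoring.** The article does not support that. It does not say that collected data are discarded, or that bed days stop being counted. Nor does it say whether non-adherers use more or fewer bed days.

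**A reader might infer that selective removal could account for the whole planned benefit.** At 20% removed and SD 10, it could not. The gap is at most 25 days (0.16 × 25² = 100), so the shift is at most 0.2 × 25 = 5.0 days, below 6. Larger artefacts arise only with more removed, or with unadjusted partial counts as in step 5.

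**A reader might infer that all loss is one-sided.** Only the rule-driven part is.

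**This is a pilot with exploratory tests.** That softens the error-rate figures. The group estimates and their intervals, which are the main output, would shift all the same.

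**Conclusion.** The point holds as a risk created by a stated rule, not as demonstrated bias. After a warning, renewed non-adherence removes a monitored participant from the study, no control can be removed on that ground, and the article does not provide for collecting outcomes afterwards. Both primary outcomes are exposed.

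The documents do not fix the size or direction. A moderate assumption gives about 2 days against a planned 6, the opposite assumption turns the sign, and crude partial counting gives about 4 days. All of these rest on an assumed 20% withdrawn under the rule. Whether withdrawals would exceed the 20% drop-out allowance cannot be settled from the article.

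**What to change.** Replace the consequence in the Home monitoring group section. Participants who meet the non-adherence criterion may stop home monitoring but remain in the study. In addition:

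- keep the 3, 6, 9 and 12-month visits, including CFQ-R, for them;
- collect bed days and antibiotic use to 12 months for everyone randomised, unless consent is withdrawn;
- analyse all randomised participants by allocated arm;
- report adherence as a process outcome, with an adherent-only analysis as a sensitivity analysis.

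The cost is one protocol sentence, one line in the information sheet and continued visits for a few participants. The estimated effect may be slightly diluted by people who stop using the equipment. The sample size need not change.

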## Outcome measures

All outcome measures will be recorded at baseline, 3, 6, 9 and 12 months, except for the semi-structured qualitative interview, which will be conducted at baseline and at 12 months (Fig. 1). Baseline data collection will include age, gender, weight (kg), body mass index (kg/m^2^), spirometry (FEV_1_, forced vital capacity (FVC)), concomitant medications, co-morbidities and health economic data. The number of courses of intravenous antibiotics and hospital admissions per year in the previous 2 years will also be recorded.

### Primary outcomes measures

The primary outcome measures are number of hospital inpatient bed days and health-related quality of life.
**Hospital inpatient days** will be defined by number of complete 24-h periods between admission and discharge.
**Health-related quality of life** will be measured by the Cystic Fibrosis Questionnaire – Revised (CFQ-R), a validated disease-specific health related quality of life questionnaire [17], which consists of 49 self-reported items within 12 domains: 1) physical functioning (8 items); 2) vitality (4 items); 3) emotional functioning (5 items); 4) eating disturbances (3 items); 5) treatment burden (3 items); 6) general health perception (3 items); 7) social functioning (6 items); 8) body image (3 items); 9) role limitations (4 items); 10) weight problems (1 item); 11) respiratory symptoms (6 items); and 12) digestive symptoms (3 items). Answers are reported on a four-point scale rating frequency, difficulty, or truth and the scores range from 0 to 100, with a higher score indicating better quality of life.

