Anecdotally we know that some patients are able to perceive a change in their symptoms better than others. Some realise that they are developing an exacerbation early on, whereas others present when they have already become more severely unwell. Additionally, patients may know that they are developing an exacerbation, but are unable to come to clinic due to other commitments or due to a lack of clinic capacity. In either case, we suspect that if we were able to diagnose the exacerbation at an earlier stage we may be more likely to be able to treat it successfully with a course of oral antibiotics, rather than intravenous antibiotics. Additionally, in our experience if the patient is less unwell they are more likely to be able to receive intravenous antibiotics at home, rather than requiring admission. This could potentially be beneficial to the patient, preventing the complications of a more severe infection and could also reduce healthcare expenditure by averting a hospital admission.

Several previous studies have assessed the effect of telehealth or home monitoring in people with CF, but the vast majority of these studies have been small feasibility studies with limited external validity [6–13]. A randomised pilot study in CF patients demonstrated that home monitoring was able to detect more pulmonary exacerbations than standard care [14]. A large randomised controlled study of home monitoring is currently ongoing in the USA, assessing the primary outcome of change in forced expiratory volume in 1 s (FEV_1_) over a 12-month period [15]. Secondary outcome measures include the effect of home monitoring on CF respiratory symptom scores, pulmonary exacerbations, health-related quality of life, treatment burden, change in prevalence of resistant strains of bacteria and adverse events. There are no cost-effectiveness analyses included in this study and no qualitative assessment of the patient experience.

The primary aims of the current study are to (1) determine whether home monitoring is effective compared with routine care in reducing hospital inpatient bed days; and (2) assess whether this results in differences in health-related quality of life over a 12 months period in adults with CF. We hypothesise that participants randomly allocated to home monitoring will require fewer hospital inpatient bed days and that they will have better health-related quality of life compared with those receiving routine care.

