### Statistical and data analysis

The outcomes listed will be summarized by group and 95% confidence intervals for these estimates will be calculated. Exploratory analyses will include basic tests to investigate differences between the intervention and control group, t-tests or chi-squared tests (or non-parametric alternative as appropriate). Cost-effectiveness will be assessed by calculating cost per reduction in hospital inpatient bed days and cost per quality-adjusted life year (QALYs) gained and appropriate sensitivity analyses will be conducted. Interview transcripts will be imported into NViVo and analysed using directed qualitative content analysis [23] to interpret meaning from the interview data in relation to the topics of inquiry, whilst allowing themes to emerge inductively from the data. To optimise rigour, data will be organized using the Framework method [24] and analysed as part of team approach, with an audit trail kept throughout. The qualitative and quantitative findings will be integrated using established methods [25] as part of the final analysis to allow us to interpret, understand and explain the trial findings.

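### The bed-day outcome drops the part-day at the end of every admission, so the absolute between-arm difference shifts slightly when admission numbers differ; elapsed hours/24 would avoid this (minor)

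*Protocol article*

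**What the plan says.** Under Primary outcomes measures, the protocol article states: "The primary outcome measures are number of hospital inpatient bed days and health-related quality of life". It then says that hospital inpatient days "will be defined by number of complete 24-h periods between admission and discharge". No separate rule is given for part-days or for stays shorter than 24 h. The words do not say that the count is made admission by admission, but measuring from admission to discharge implies it.

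The Sample size section gives the planning values: "Estimating the mean number of hospital inpatient days is 42 for those receiving standard care and 36 for those receiving monitoring". With an SD of 10 and 40 patients in each arm, it adds that "approximate 95% confidence intervals for these estimates would be (39, 45) and (33, 39) respectively". It does not say over what period these means are taken or which counting rule lies behind them.

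Two other places bear on the point. The Background section expects that "if we were able to diagnose the exacerbation at an earlier stage we may be more likely to be able to treat it successfully" by oral rather than intravenous antibiotics. It also expects that some patients could have intravenous treatment at home instead of being admitted. The Statistical and data analysis section carries the count into the economics: "Cost-effectiveness will be assessed by calculating cost per reduction in hospital inpatient bed days".

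**The concern.** A bed-day count should reflect the time a bed is occupied. Under this rule, a patient admitted on Monday at 16:00 and discharged on Tuesday at 11:00 has used a bed overnight and scores 0. One discharged on Wednesday at 11:00 has stayed two nights and scores 1. What is lost is a fraction of a day per admission, whatever the length of stay.

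If both arms had the same number of admissions and similar admission and discharge times, the loss would drop out of the difference. Here the number of admissions lies on the causal path, because averting admissions is one way the intervention is meant to work. The rule can therefore move the estimated effect on a primary outcome, and it moves the denominator of the cost ratio by the same amount. The Secondary outcome measures section records the costs of inpatient admissions, so a stay under 24 h would add cost while adding no bed days.

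**Working it through.** **Inputs from the protocol article.** Means 42 and 36 days, SD 10, 40 patients per arm (Sample size); randomisation strata running from 1–2 to more than seven intravenous-antibiotic admissions in the preceding 24 months (Recruitment and randomisation).

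**Inputs assumed, because the article does not give them.** Length of stay 10 to 14 days; mean part-day lost *f* = 0.5 day (uniform), with 1 day as the limit; 42 and 36 taken as true 12-month means in elapsed days. The strata suggest up to about 4 admissions a year for most patients, and 42/4 = 10.5 days, so stays of about 10 days or more fit the planning mean.

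1. **The plan's own figure.** 1.96 × 10/√40 = 3.10. This gives 42 ± 3.10 = (38.9, 45.1) and 36 ± 3.10 = (32.9, 39.1), which match the stated intervals after rounding. For the difference between arms, the half-width is 1.96 × 10 × √(2/40) = 4.38 days.

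2. **Formula.** Let *T* be true mean days per patient and *A* mean admissions per patient, with subscripts c (control) and m (monitoring). The counted mean is *T* − *A*·*f*, so

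   counted difference = (*T*c − *T*m) − (*A*c − *A*m) × *f*.

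   A one-admission difference therefore shifts the result by 0.5 day (0.5/6 = 8%), with a limit of 1 day (1/6 = 17%).

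3. **Expected mechanism: fewer admissions of unchanged length.**
   - 14-day stays: 42/14 = 3.00 against 36/14 = 2.57 admissions, a difference of 0.43. Counted difference: 6 − 0.43 × 0.5 = 5.79; at the limit, 6 − 0.43 = 5.57.
   - 10-day stays: 4.2 against 3.6 admissions, a difference of 0.6. Counted difference: 6 − 0.6 × 0.5 = 5.70; at the limit, 6 − 0.6 = 5.40.

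   The understatement is 0.2 to 0.3 day at *f* = 0.5, and 0.4 to 0.6 day at the limit.

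4. **Cost ratio.** With the cost difference held fixed, the ratio is inflated by 6/5.79 = 1.04 to 6/5.40 = 1.11, that is, by about 4% to 11%.

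5. **Simulation check.** With Poisson admissions, gamma-distributed stays of mean 10 days and admission times uniform over the day, the true difference was 5.95, the 24-h rule gave 5.66 and counting midnights gave 5.95. Only 0.08% of the simulated stays were under 24 h.

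6. **Midnights are not the same as elapsed time.** Suppose instead that admissions fall uniformly at 12:00–20:00 and discharges at 09:00–14:00 (assumed). Midnights then exceed elapsed days by (16.0 − 11.5)/24 = 0.19 per admission. The 24-h rule loses 0.95 day per admission against midnights and 0.95 − 0.19 = 0.76 against elapsed time. The agreement in step 5 depends on uniform admission times.

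7. **Hypothetical reverse case: more, shorter admissions under monitoring.** For 3 × 14 against 4 × 9 days, the counted difference at *f* = 0.5 is (42 − 1.5) − (36 − 2.0) = 6.5; at the limit it is 39 − 32 = 7.0. Here the benefit is exaggerated.

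**The case against.** The best defence is that this is a definition, not an error. It is objective, fixed in advance, the same in both arms of an unblinded trial, and contradicted nowhere in the article. The effect is a fraction of a day against a confidence-interval half-width of 4.4 days, and under the expected mechanism it works against the intervention. The study is titled a pilot and its between-arm tests are called exploratory. A relative comparison is also untouched when days and admissions fall in proportion: with 14-day stays, (36 − 2.57 × 0.5)/(42 − 3 × 0.5) = 34.71/40.5 = 0.857, the same as 36/42.

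Most of this stands, and it is why the point is minor. Two things remain. The planned cost ratio uses the absolute reduction, which does shift. And a systematic shift does not shrink with sample size, so comparing it with sampling error limits its importance without removing it.

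A reader might go further and infer that the rule inflates the apparent benefit substantially, or hides many short admissions. The protocol does not support either reading. Inflation needs monitoring to produce more and shorter admissions, whereas the Background section predicts averted ones. A figure as high as +50% (3 × 14 against 6 × 6 days, counted as 39 − 30 = 9.0) needs doubled admissions and a loss of a full day per admission, which elapsed time can only approach. As for short stays, the article gives no length-of-stay distribution. If 42 days is an annual mean, the strata point to long stays.

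**Conclusion.** The concern holds as a minor one. The stated rule truncates every stay that is not an exact multiple of 24 h and scores stays under 24 h as zero. The absolute bed-day difference therefore moves by the part-day lost times the between-arm difference in admissions per patient: about 0.5 day, and at most 1 day, per one-admission difference.

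If monitoring averts admissions as expected, the planned 6-day benefit would be counted as about 5.4 to 5.8 days, a small and conservative error. The direction would reverse only if monitoring led to more, shorter admissions, which is possible but not predicted by the protocol.

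These sizes rest on assumed stays of 10 to 14 days, a part-day lost of 0.5 to 1 day that is equal in the two arms, and reading 42 and 36 as 12-month elapsed days. If admission or discharge times of day differed between arms, a shift could arise even with equal admissions. Nothing here makes the outcome unusable.

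**What to change.** Under Primary outcomes measures, define hospital inpatient days as the sum, over all of a participant's admissions in the study period, of the time from admission to discharge in hours divided by 24, with fractions kept and the same calculation in both arms. Use that count in the cost per reduction in bed days.

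Report the number of admissions per arm beside it; the Abstract already lists hospital admissions among the effects to be assessed. Midnights in hospital can be given as a sensitivity count, with a note that they can exceed elapsed time and are not interchangeable with it.

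The cost is one sentence in the definition. Counting complete 24-h periods already requires admission and discharge times, so nothing new has to be collected. If data are already in hand, the count can be recomputed from those times, with the published version shown alongside.
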